### Randomisation and blinding

As mentioned above, randomization will be done in a time-dependent manner (in four-week blocks) in order to avoid the confounding variable of participants in the control group seeing subjects in the treatment group performing physical activity in addition to normal hospital care. Participants will be explicitly informed and reminded not to discuss their randomisation assignment with assessment staff. The assessment staff will be blinded to participant randomisation assignment, as well as to the main study design and to what changes we expect to occur in the study outcomes in either group. Because blinding of assessment staff to participant randomisation assignment might not be actually feasible in all cases due to the time-dependent manner of randomisation, we will record blinding success and add it as a covariate in the analyses (see below). It will not be possible to conceal the group assignment from the staff involved in the training of the intervention group.

### Sample size and statistical power

The required sample size was determined for one of the primary outcome variables, i.e. the SPPB. We believe that a clinically relevant change is a ≥30% increase in the aforementioned test battery. We expect the control group to improve ~0 to 5%; thus, we can detect differences of at least ≥35% with a power >80% and a level of significance of 0.05 with two groups of 60 subjects. Assuming a maximum loss of follow-up of 20%, we will recruit a total of 150 patients.

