### Statistical analysis

To assess the training effects on the study outcomes, we will analyze the data according to the intention-to-treat principle [37]. When post-test data are missing, baseline scores will be considered post-test scores. We will use a two-factor (group and time) analysis of variance (ANOVA) with repeated measures. We will repeat the analysis using the actual blinding of assessment staff to participant randomisation assignment (successful or not), baseline values of age, body mass index, MMSE, number of falls within the previous year and handgrip strength as covariates. For each outcome variable we will report the level of significance corresponding to the main group (between-subjects), time (within-subjects) and interaction (group × time) effects. We will perform post hoc pre- vs. post comparisons by group only when a significant group*time effect is present. The level of significance will be set to = 0.05. We will adjust multiple comparisons for mass significance [38]. We will use the Student’s *t* test (or its non-parametric equivalent, the Mann Whitney’s *U* test) for comparing between the two groups the mean values of those secondary outcomes that will be assessed only once, i.e. three months after discharge (number of falls, Katz score and Barthel index). We will compare mortality rate at three months after discharge in the two groups with the chi square test.

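### The sample-size paragraph derives a detectable SPPB difference of at least 35%, but its own inputs, read as changes within each group, give 25 to 30%

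*Protocol article*

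**What the plan says.** All of the sizing is in the protocol article under Sample size and statistical power. The calculation is based on the SPPB: "The required sample size was determined for one of the primary outcome variables, i.e. the SPPB". The relevant effect is given as a relative change: "We believe that a clinically relevant change is a ≥30% increase in the aforementioned test battery". It is not said whether this is a gain within the trained group or a difference between groups.

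The control assumption and the conclusion drawn from it follow in one sentence: "We expect the control group to improve ~0 to 5%; thus, we can detect differences of at least ≥35" per cent, "with a power >80% and a level of significance of 0.05 with two groups of 60 subjects". With a 20% allowance for loss to follow-up, 150 patients are to be recruited. No SD is given, the test is not said to be one- or two-sided, and power is given only as a lower bound.

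**The concern.** The three percentages are joined by *thus*, so the 35% is presented as a consequence of the other two. It does not follow from them. If trained patients gain 30% and controls gain something, the groups differ by less than 30, not by more.

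This is the only justification for 60 per group. If the power claim is attached to 35 points while the plan's inputs imply 25 to 30, the trial's power for the effect it expects is lower than stated. A non-significant result could then be read as evidence against a relevant effect on the strength of a power figure that applies to a larger one.

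**Working it through.** Below, *points* means percentage points of SPPB change, not units of the 0 to 12 score.

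**Inputs from the section:** relevant increase 30%; control improvement 0 to 5%; stated detectable difference 35%; power above 80%; significance level 0.05; 60 per group; 20% loss.

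**Assumptions:** two-sided test; two-group comparison of mean percentage change; SD not given, so solved back from the stated power.

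**Step 1. Recruitment figure.** 2 × 60 = 120, and 120 / (1 − 0.20) = 150. This reproduces.

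**Step 2. The difference.**
- Both figures as within-group gains: 30 − 0 = 30 and 30 − 5 = 25, so 25 to 30 points. The stated 35 needs 30 + 5.
- Controls meant to decline by 0 to 5%: 30 − (−0) = 30 and 30 − (−5) = 35, so 30 to 35 points. The sign of the control change is then wrong in the text, and 35 is the most favourable end of the range.
- 30% meant as the between-group difference: over a 5% control gain the trained group must gain 30 + 5 = 35%. The arithmetic is then right, but 35% is a within-group gain and is mislabelled as a difference.

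**Step 3. The stated power.** It cannot be reproduced independently, because there is no SD. The SD implied by a given power at 35 points is

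SD = 35 / [(1.960 + z_power) × √(2/60)], with √(2/60) = 0.1826.

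For 80% power: SD = 35 / (2.802 × 0.1826) = 68.4 points, a standardised difference of 0.51.

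**Step 4. Power at the implied difference.** Power(Δ) = Φ[Δ / (SD × 0.1826) − 1.960].

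Worked case (80% at 35 points):
- Δ = 30: 2.802 × 30/35 = 2.401; 2.401 − 1.960 = 0.44; power 67%.
- Δ = 25: 2.802 × 25/35 = 2.001; 2.001 − 1.960 = 0.04; power 52%.

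| Power at 35 points | Implied SD (points) | Power at 30 | Power at 25 |
|---|---|---|---|
| 80% | 68.4 | 67% | 52% |
| 85% | 64.0 | 73% | 57% |
| 90% | 59.1 | 79% | 64% |
| 95% | 53.2 | 87% | 73% |

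A noncentral t calculation of the 80% row also gives 67% and 52% (SD 67.9). A one-sided test calibrated to 80% at 35 points gives 69% and 55%.

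**Step 5. The mislabelling reading.** If the powered difference is 30 points, the stated power above 80% applies there. If it is exactly 80% at 30, then at 25 points 2.802 × 25/30 = 2.335; 2.335 − 1.960 = 0.375; power is about 65%.

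**The case against.** The strongest reply is that the section never says whether 30% is a within-group gain or a net difference. If it is the net difference, adding 5 is correct, the fault is one loosely used word, and power for the relevant effect is above 80% as claimed. This stands as a possible reading, so it cannot be asserted that the trial is sized for more than it calls relevant. It does not clear the sentence, because the text says *differences*, and on this reading that word is wrong.

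Second, the protocol says above 80%, not 80%. A reader might infer from the first row of the table that a relevant effect would be missed in a third to a half of such trials. The documents do not support that as a fact. It holds only if power at 35 points is exactly 80%, two-sided. At 90%, the chance of missing a 30-point difference is about 21% (100 − 79).

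Third, an article may leave the SD to the full protocol, so its absence is not counted here as a fault of its own. It only explains why power at 25 to 30 points has to be given as a range.

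Fourth, a reader might go further and argue that, because the SPPB is one of two primary measures and "We will adjust multiple comparisons for mass significance", power should be computed at half the significance level. The Statistical analysis section does not say that this adjustment covers the two primary measures, and it sets no split. That step would be an assumption added from outside.

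**Conclusion.** The point holds as an internal inconsistency. A 30% increase against a control improvement of 0 to 5% does not lead to a difference of at least 35%. Taken as within-group changes, the inputs give 25 to 30 points, and each of the other two readings also requires a correction: the sign of the control change, or the label on the 35%.

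The effect on power is conditional. It rests on the literal reading, a two-sided 0.05 test, 60 evaluable patients per group and an SD back-solved from the stated power. On those terms power lies between 67% and 87% at 30 points, and between 52% and 73% at 25 points, as power at 35 points runs from 80% to 95%. Power at 30 points reaches 80% only if power at 35 points is about 90% or more.

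A reader might infer that the trial is shown to be underpowered and must be enlarged. With the 68.4-point SD, 80% power would need 82 per group for 30 points and 118 for 25. That SD is not the protocol's, so the documents do not establish the need.

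**What to change.** In the section on sample size and statistical power:

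1. State whether the 30% is a gain within the trained group or a difference between groups.
2. Make the three percentages agree. Either give the between-group difference as 25 to 30%, or correct the sign of the expected control change, or relabel the 35% as the trained group's gain.
3. Restate the power of 60 per group for that difference, with the SD used, the exact power and whether the test is one- or two-sided.

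The cost is a rewritten paragraph and possibly a lower stated power. No extra patients are needed to make the correction, and both primary outcomes stay as they are.

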### Usual care group (control)

Participants randomly assigned to the usual care group will receive normal hospital care, which includes little physical activity, i.e. short daily walk in all patients at risk for delirium or functional decline.

### Intervention (training)

The intervention will consist of strength training of the lower body and walking. Both types of training will be performed three times per day during the week (Monday to Friday), two times per day on Saturday, beginning as soon as possible after admission and continuing until discharge. No training will take place on Sunday. Training sessions will be dispersed throughout the day. When three sessions per day are performed, one will take place between 9–11 a.m., one between 13–15 p.m., and the last one between 17–19 p.m.; when two sessions per day are performed training will take place during the first two of the aforementioned time periods. Strength training will be performed first, and followed by walking. A rest period of up to five minutes will be allowed between the strength and walk training.

Strength training will consist of rising from a seated position in a chair to an upright position with or without the use of the subject’s hands on the armrests of the chair. Initially 10 repetitions or as many repetitions as possible up to 10 of rising from a seated position will be performed each training bout. The strength training will be progressed from one set of the 10 repetitions to 2 and then 3 sets of the 10 repetitions based on individual progress. When a patient can perform one set of 10 repetitions for all three training bouts on two consecutive days a second set will be added. When a patient can perform two sets of 10 repetitions for all three training bouts on two consecutive days a third set will be added.

Completion of one set of 10 repetitions of strength training should take approximately one-two minutes. A two-minute rest period will be allowed between strength training sets if more than one set is performed. If a subject completes three sets of strength training total training time will be between 7 and 10 minutes.

Walk training will consist of walking as far as possible with or without assistance for 10 minutes. Total length of each training session will be 20–23 minutes. During the week when three training sessions per day are performed total training time per day will be 60–69 minutes. On Saturdays when two training sessions per day are performed total training time will be 40–46 minutes. All training sessions will be individually monitored with a record of training completed compiled.

### Participant retention and adherence

To reduce participant drop out and to maintain adherence to the training program, the potential benefits of performing the training will be explained to subjects in the intervention group. Qualified fitness specialists will individually monitor and carefully supervise all training sessions and provide instruction and encouragement during all training sessions. Distribution of the training sessions throughout the day should minimize cumulative fatigue and so help maintain adherence. Adherence to the exercise intervention program will be checked in a daily register of sessions.

### Demographics

A standard questionnaire including name, residence, age, reason for hospitalisation, medical history, current dosage of medications being taken and history of falls in the last year will be administered by trained investigators.

### Primary outcome (functional capacity) measures

The Short Physical Performance Battery (SPPB) will be used to assess participants’ physical ability at baseline (admission) and discharge. The SPPB consists of performance of three different tests (repeated chair stand test, time needed to walk a distance of 4 meters two times, and a hierarchical standing balance test), with the scores on all three tests combined resulting in a composite, continuous score of 0 to 12, as explained below [26]. The repeated chair stand test consists of rising from and sitting in a chair five consecutive times whereas the walking test consists of walking 4 meters two times with or without the assistance of a cane or walker. Scoring in each of the aforementioned two tests is done on a 0–4 point scale, where those who cannot complete the task are assigned a score of 0 and those completing the task are assigned a score of 1 to 4, corresponding to the quartiles of time needed to complete the task, with the fastest times scored as 4 [26]. For the hierarchical standing balance task, participants are first asked to place their feet in a side-by-side position, followed by a semitandem position (heel of one foot along side the big toe of the other foot) and tandem position (heel of one foot directly in front of the other foot) [27]. Participants are required to hold the side-by-side position for 10 seconds to advance to the semitandem task, and to advance to the tandem task the semitandem position must be held for 10 seconds. Those who cannot hold the side-by-side position for 10 seconds are assigned a score of 0 whereas those who can hold it for 10 seconds but are unsuccessful in holding the semitandem position for 10 seconds receive a score of 1. A score of 2 is given if the semitandem is held for 10 seconds but the tandem cannot not be held for more than 2 seconds, a score of 3 is given if the tandem is held for 3–9 seconds, and a score of 4 if the tandem is held for 10 seconds. The total score for the SPPB is the sum of the score on all three tests, i.e. in a continuous 0–12 point scale.

Time to walk 10 meters will be also determined as a test of the participants’ functional capacity at baseline (admission) and discharge. The participant will be asked to ambulate 10 meters as quickly as possible with or without assistance from a cane or walker.

All SPPB and 10-meter walk tests will be administered by the same investigator with time determined to the nearest 0.1 second.

### Secondary outcome measures

#### *Length of hospitalization*

We will assess length of hospitalization (in days).

#### *Pulmonary ventilation*

Pulmonary ventilation is negatively affected by aging due to decreased ability to expand the rib cage resulting in an increased lung residual volume [28]. The inability to expand the rib cage is exasperated with bed rest, which can eventually affect the ability of the pulmonary system to exchange oxygen and carbon dioxide [29,30]. Pulmonary ventilation will be assessed at admission and discharge as forced expiratory volume in one second (FEV_1_). To measure FEV_1_ the patient will be asked to inhale maximally and then exhale maximally while in a seated position into a hand held flow meter (Flow Screen, Jaeger Company, Viasys Healthcare GmbH, Germany).

#### *Peripheral oxygen saturation*

Peripheral oxygen saturation (SpO_2_) decreases from approximately 85 to 77 mmHg in seniors when moving from a standing to a supine position [31]. Such decreases can result in symptoms of confusion in patients already at the threshold of pulmonary insufficiency [28]. Physical activity also results in a decrease in partial pressure of oxygen. SpO_2_ will be determined at admission and discharge, immediately pre and immediately post of the 10-meter walk test using a finger pulse oximeter (Rossmax Inno Tek Corp, Taiwan).

#### *Assessment after discharge*

We will perform a follow-up phone interview with participants (or their relatives/caregivers in case of death) three months after discharge, to determine mortality rate after three months and number of falls within three months after discharge, and also to subjectively assess the ability to cope with ADLs using the Katz ADL score [24] and the Barthel ADL index [25].

The Katz ADL scale includes six items (eating, transferring from bed to chair, walking, using the toilet, bathing, and dressing) each of which is scored with 0 (= unable to perform the activity without complete help), 0.5 or 1.0 (= able to perform the activity with little help or without any help, respectively) [24]. A sum-score (ranging from 0 to 6) is given for each patient. The Barthel index is an instrument widely used to measure the capacity of a person for the execution of ten basic activities in daily life, obtaining a quantitative estimation of the subject’s level of independency [25,32]. The ten items include: eating, transferring from bed to chair, using the toilet, bathing/showering, personal hygiene (e.g., tooth brushing, shaving) dressing, walking, stair climbing, and bowel and bladder control. Each individual item is scored with 0 (i.e. unable to perform without complete help or fecal/urine incontinence), 5 (i.e. able to perform the activity with little help or only accidental fecal/urine incontinence) or 10 (i.e. able to perform without any help or total fecal/urine continency). The sum-score ranges from 0 (*totally dependent*) to 100 (*totally independent*).

### Covariates

Besides actual blinding success of assessment staff to participant randomisation assignment, the following covariates will be measured in all participants upon hospital admission as they could influence one or more of the study outcomes.

#### *Body mass index*

Standing height will be measured to the nearest 0.1 cm with a clinical stadiometer (Asimed T2, Barcelona, Spain) while the person is standing barefoot. Body mass will be determined to the nearest 0.05 kg using a balance scale (Ano Sayol S.L., Barcelona, Spain) with the person in her/his underwear. Body mass index (BMI) will be calculated as weight/height (kg/m^2^).

#### *History of falls within the previous year*

We will record the participants’ history of falls within the 12-month period prior to hospital admission. A fall will be defined as an “unexpected event in which the participants come to rest on the ground, floor, or other lower level” [33,34].

#### *Maximal handgrip strength*

Handgrip strength will be measured using a digital dynamometer (T.K.K. 5101 Grip-D; Takey, Tokyo, Japan), with the scores recorded to the nearest 0.1 kg. When performing the measurement, participants will be instructed to maintain the standard bipedal position during the entire test with the arm at their side in complete extension. The dynamometer will not be allowed to touch any part of the body except the hand being tested. Each subject will perform (alternately with both hands) the test twice with a 30–60 second rest period between the measurements. For each measure, the hand to be tested first will be chosen randomly. The grip span of the dynamometer will be adjusted to the individual’s hand size [35].

#### *Cognitive ability*

The Mini-Mental State Examination (MMSE) will be administered to determine participants’ cognitive ability [36].

### Familiarization and reliability assessment

Before the start of the study all subjects will have a familiarization session consisting of an explanation of all tests and performing all tests. This session will last ~30 minutes. Test-retest reliability for each outcome measure will be determined on a sub-population of the subjects.

### Assessment of side effects

Adverse events, including muscle pain, fatigue, and general aches and pains will be recorded by the training and testing staff; and by self-report during the study period. We will also record the falls during the study. An independent researcher will be in charge of auditing all nursing and medical records to record all falls in the participants during the study period.

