## Methods/Design

### Study design

The present study is a randomised controlled trial (RCT) (ClinicalTrials.gov ID: NCT01374893) and is designed to be compliant with the recommendations of the Consolidated Standards of Reporting Trials (CONSORT) statement [23]. The study flow diagram is shown in Figure 1. After signing an informed consent form subjects will be randomly assigned (as explained below) to either the intervention or control group. The intervention group will perform the multi-session per day training program while the control group will receive normal hospital care. Due to the possible effect of subjects in the control group seeing subjects in the intervention group performing physical activity in addition to normal hospital care, randomization will take place in a time dependent manner. Patients admitted during four-week blocks of time will all be assigned to either the treatment or control group, with a one week period between four-week periods. The participants will be followed for the length of their hospital stay, and also with a follow-up phone interview three months after discharge to determine mortality rate at three months, number of falls since discharge, and to subjectively assess the ability to cope with ADLs using the Katz ADL score [24] and the Barthel ADL index [25].

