**Figure 1 F1:**
[figure not shown]
Study flow diagram.

All testing (at admission and discharge) will be performed in the same setting (*Hospital General Universitario Gregorio Marañón*, Madrid, Spain) and by the same investigators. The study will be performed between June 2012 and June 2013, following the ethical guidelines of the Declaration of Helsinki, last modified in 2000.

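### Having testing staff record muscle pain and fatigue opens an avoidable route by which the assessor of both primary outcomes can learn the arm

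*Protocol article*

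**What the plan says.** Under Randomisation and blinding, the protocol article sets the rule for assessors: "The assessment staff will be blinded to participant randomisation assignment, as well as to the main study design". They are also kept unaware of the changes expected in either group. A second safeguard concerns the patients: "Participants will be explicitly informed and reminded not to discuss their randomisation assignment with assessment staff". The section concedes that blinding may not be achievable in every case, gives the time-block allocation as the reason, and says that blinding success will be recorded and used as a covariate. Statistical analysis carries this through as a repeat of the main analysis.

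Under Assessment of side effects: "Adverse events, including muscle pain, fatigue, and general aches and pains will be recorded by the training and testing staff". Self-report is a further source, and an independent researcher audits nursing and medical records for falls.

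Two other statements bear on the point. Primary outcome (functional capacity) measures says "All SPPB and 10-meter walk tests will be administered by the same investigator with time determined to the nearest 0.1 second". Study design says "Patients admitted during four-week blocks of time will all be assigned to either the treatment or control group". The same section leaves a gap of one week before each new block.

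The article nowhere distinguishes testing staff from assessment staff, and nowhere separates the recording of complaints from outcome testing.

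**The concern.** Muscle pain and fatigue are complaints one would expect from repeated chair rises and ten-minute walks up to three times a day. When a tester takes such a complaint, the natural next remark is its cause, and that is what patients are asked not to reveal. The recording duty therefore works against the blinding rule.

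At stake are both primary outcomes. The SPPB and the 10-metre walk depend on the patient's effort, and the balance score depends on whether a position counts as held for ten seconds. A tester who knows the arm can, without intending it, encourage more or judge more leniently in the direction of the hypothesis.

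The design can amplify a single disclosure, because the same person tests everyone and neighbouring patients share an arm.

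**Working it through.** **The statements side by side.** Assessors must not know the arm; patients must not discuss it with them; testing staff record the complaints that training is likely to cause; one investigator tests both primary outcomes; all patients in a block share an arm. The first two conflict in practice with the third, and the last two determine how far a disclosure might reach.

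**Size, as an illustration.** The article gives no disclosure rate, so the rate below is an assumption shown over a range.

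1. *Patients.* Sample size and statistical power gives two groups of 60 and 20% loss. 120 / (1 − 0.20) = 150, which reproduces the stated total.
2. *Blocks.* Four weeks plus a one-week gap make a five-week cycle. June 2012 to June 2013 is taken as about 52 weeks. Since no gap is needed after the last block, (52 + 1) / 5 = 10.6 blocks.
3. *Patients per block.* 150 / 10.6 = 14.2, so n is about 14. For 48 to 56 weeks the range is about 15 down to 13.
4. *Share tested after an earlier patient's disclosure.* Let p be the chance that a training patient reveals the training to the tester. Suppose patients are tested in sequence and one disclosure reveals the rest of the block. The expected share is 1 − [1 − (1 − p)^n] / (n p).
   - p = 0.05: 1 − 0.512 / 0.70 = 0.27
   - p = 0.10: 1 − 0.771 / 1.40 = 0.45
   - p = 0.20: 1 − 0.956 / 2.80 = 0.66
5. *Trial-wide share.* Control patients have no training to mention, so the route operates only in training blocks, taken as half the patients. Halving gives about 13%, 22% and 33%.
6. *Counting the disclosing patient's own discharge test as well.* The training-block shares become 31%, 50% and 73%.
7. *No spread to other patients.* If each disclosure reveals only that patient's arm, the training-block share is p itself: 5%, 10% or 20%.

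**Whether the covariate repairs it.** Blinding success is determined after allocation, and by this route it fails only in training blocks. It is therefore entangled with arm and block. Adjusting for it cannot cleanly separate assessor bias from a training effect.

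**The case against.** The strongest reply is that the text contains no outright contradiction. Testers are not told to question patients, and each group of staff may simply note what arises in its own sessions. Pain and fatigue are also common in acutely ill patients over 75 under usual care, so a complaint alone reveals nothing; the patient has to name the training. This stands. The point is a tension between two duties that the text leaves unmanaged.

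A reader might infer that one complaint unblinds the rest of a block. The article does not support that as a certainty, because assessors are meant to be blind to the main study design and so should not know that blocks are single-arm. One tester working through about ten blocks would probably notice, but that is an inference.

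A reader might also take recording of blinding success to be the only safeguard. It is not: patients are instructed, and assessors are kept from the design and the expected changes.

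The person testing the SPPB need not be the person recording complaints, since other tests exist and the article speaks of several investigators. The wording allows this but does not require it.

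Finally, the article already concedes imperfect blinding, and visible training or casual remarks could reveal the arm anyway. That is true, and what the complaint route adds to this risk cannot be isolated from the document. But the concession names only the time blocks, which are inherent in the design. The recording duty is a separate route that can be removed.

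**Conclusion.** The concern holds in limited form. Giving testing staff the recording of exercise-type complaints creates an avoidable disclosure route to the assessor of both primary outcomes, and the planned covariate does not cleanly repair it. A disclosure unblinds at least that patient's discharge tests; it may, but need not, inform later tests in the same block.

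The shares of 27%, 45% and 66% describe training blocks only and should not be read as shares of the whole trial, where they are about 13%, 22% and 33%. They rest on assumed disclosure rates of 5%, 10% and 20%, about 14 patients per block, tests in sequence, and a tester who generalises from one patient to the block. They measure exposure to knowledge of the arm; nothing in the document allows the resulting bias in SPPB points or seconds to be estimated. The sample size is unaffected. This is a cheap improvement worth making.

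**What to change.** Reword Assessment of side effects so that the investigator who gives the SPPB and 10-metre tests neither solicits nor records complaints. Have them collected in the same way in both arms by existing staff who do not test the primary outcomes. One option is to take them from ward nursing records by widening the record audit already planned for falls. Keep the information from the tester for the whole study. Events seen during a test are still noted.

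Letting the tester ask once a patient's discharge scores are closed would not be enough, because the answer could still inform that tester about later patients in the block. No change to test scheduling is needed for this defect.

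The cost is slightly more work for ward staff or the record auditor, and possibly less detailed symptom capture.

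### Non-fall adverse events have an extra, unblinded recording channel in the training arm only, so any counts by arm would not be fully comparable

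*Protocol article*

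**What the plan says.** All places are in the protocol article.

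- **Assessment of side effects** names three channels for adverse events. Muscle pain, fatigue and general aches are the examples given, and they "will be recorded by the training and testing staff; and by self-report during the study period".
- The same section gives falls a further source: an independent researcher is charged with "auditing all nursing and medical records to record all falls in the participants during the study period". No such audit is described for other events.
- **Participant retention and adherence**: "Qualified fitness specialists will individually monitor and carefully supervise all training sessions".
- **Intervention (training)** sets the frequency: "Both types of training will be performed three times per day during the week (Monday to Friday), two times per day on Saturday". It adds: "No training will take place on Sunday".
- **Randomisation and blinding** says of the trainers: "It will not be possible to conceal the group assignment from the staff involved in the training of the intervention group". Of the testers it says: "The assessment staff will be blinded to participant randomisation assignment". It also concedes that tester blinding may fail because allocation goes by calendar block, and it plans to record whether blinding succeeded.
- **Usual care group (control)** describes ordinary hospital care and no study sessions.
- **Study design** places the testing of both groups at admission and at discharge.
- **Statistical analysis** names no between-group comparison of adverse events.

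**The concern.** Muscle pain, fatigue and aches are minor complaints, and how many are recorded depends heavily on who is present and how often. Here one recording channel operates in one arm only, several times a day, through staff who know the allocation. The channels shared by both arms are less intensive on the staff side, since the testers' planned assessments are at admission and discharge.

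If events from all three channels are added up and shown by arm, the trained arm would tend to look worse even if training caused no extra events. The article's Discussion says that the study examines the feasibility as well as the effect of training, so a spurious excess of side effects could count against the programme. The problem arises at data collection: unless the source of each event is recorded, no later analysis can separate the channels.

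**Working it through.** **1. Contact with training staff.** The inputs are from the Intervention (training) section: 3 sessions a day Monday to Friday, 2 on Saturday, none on Sunday, each lasting 20–23 minutes.

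- The article's own daily figures are reproduced: 3 × 20 to 3 × 23 = 60–69 minutes on weekdays, and 2 × 20 to 2 × 23 = 40–46 minutes on Saturday.
- Sessions in a full week: 3 × 5 + 2 × 1 + 0 = 17.
- Supervised time in a full week: 5 × 60 + 40 = 340 to 5 × 69 + 46 = 391 minutes.
- Upper limit for a 14-day stay (the maximum in the Abstract): 2 × 17 = 34 sessions.
- Contacts with training staff described for controls: 0.

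**2. Channels by arm.**

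| Source | Training arm | Control arm |
|---|---|---|
| Training staff (allocation known) | every session, up to 17 a week | none described |
| Testing staff | admission and discharge | admission and discharge |
| Self-report in the study period | yes | yes |
| Independent record audit | falls only | falls only |

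The first row is the only one that differs. The inequality is therefore partial. For falls, the audit gives a source that is the same in both arms.

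**3. Possible size.** The documents give neither event rates nor detection probabilities, so what follows is illustration. Let the true risk p be equal in both arms, and let d_C and d_T be the probabilities that an event is recorded in the control and training arms. The observed risks are p·d_C and p·d_T, so the observed risk ratio is d_T / d_C, whatever p is.

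The last column gives the chance that a two-sided 5% comparison of two proportions would show a significant excess in the training arm. It uses 60 per arm (Sample size and statistical power section) and p of 20% and 30% (assumed). It applies the normal approximation Φ{[|p_T − p_C|√n − 1.96√(2p̄(1 − p̄))] / √(p_C(1 − p_C) + p_T(1 − p_T))}, where p_C and p_T are the observed risks and p̄ is their mean.

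| d_C | d_T | Observed risks, p = 20% | Observed risks, p = 30% | Risk ratio | Chance of a significant excess, p = 20% / 30% |
|---|---|---|---|---|---|
| equal | equal | equal | equal | 1.00 | 2.5% / 2.5% |
| 0.80 | 0.90 | 16% v 18% | 24% v 27% | 1.13 | 4.8% / 5.7% |
| 0.60 | 0.90 | 12% v 18% | 18% v 27% | 1.50 | 14.8% / 21.7% |
| 0.40 | 0.90 | 8% v 18% | 12% v 27% | 2.25 | 36.9% / 54.6% |

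The direction is the same whenever d_T exceeds d_C. The size ranges from slight to large and depends wholly on the assumed detection probabilities.

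**The case against.** The strongest reply has four parts.

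- **No comparison is planned.** Adverse events are neither a primary nor a secondary outcome, and the Statistical analysis section gives no test for them. The side-effects section can be read as monitoring of the training. This stands. A reader might infer that the trial's safety comparison is biased, but the article plans none that could be. The point concerns any by-arm counts that are later reported, and untested counts would carry the same distortion.
- **Two of the three channels, and the falls audit, cover both arms.** This also stands, and it limits the point to a partial inequality for non-fall events. It does not remove it, because an added channel in one arm still makes the totals unlike.
- **An article condenses the full protocol.** Forms, questions and reporting layout may well be settled elsewhere, and their absence here is no fault. But the point rests on what the article does state: who records events, and that the common audit is for falls.
- **Blinding is already addressed.** A reader might infer that testers who record soreness are thereby unblinded before the discharge tests. The article does not support that. It states no order of questioning, and fatigue or aches in hospitalised patients of this age need not reveal allocation. Participants are told not to disclose their group, and blinding success is recorded and used as a covariate. What remains is a possible extra route to unblinding, which merits a precaution only.

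Trainers should of course record what they see. The objection is only to mixing their records into a comparison between arms.

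**Conclusion.** The point holds in a limited form and is minor. Recording of non-fall adverse events is partly unequal by arm: the training arm has an additional, unblinded channel of up to 17 sessions a week with no counterpart in controls. By-arm counts would tend to be higher with training even under equal true rates. It is not certain that they will be, since the tendency rests on the reasonable assumption that frequent supervision picks up more minor complaints.

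The size cannot be derived from the documents. The range of about 1.13 to 2.25 for the observed risk ratio rests on assumed detection of 80% down to 40% in controls against 90% in training, and no single value in it should be read as an estimate. The audited fall counts are not affected by this inequality, although falls noted only by trainers would be if they were added to them. The primary outcome analysis is not shown to be affected.

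**What to change.** 1. Record the source of every adverse event: training staff, testing staff, self-report or record audit.
2. Base any between-arm comparison of non-fall events only on sources common to both arms. These are self-report during the stay and at discharge, taken with the same questions in both arms, and the independent record audit, extended from falls to all adverse events.
3. Report trainer-recorded events separately, as a description of the intervention arm.
4. As a precaution for blinding, have testing staff ask about adverse events at discharge only after the SPPB and the 10-metre walk.

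The cost is a few sentences of wording, one extra data field and somewhat more extraction by the researcher who already audits the records. The downside is that minor events seen only by trainers leave the comparison, which becomes less sensitive. They are still reported under item 3.
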